### **\*Complications possibly related to enteral feeding**

Digestive intolerance: either vomiting, tracheal aspiration of enteral feeding (defined in 7), diarrhea, or gastric residue above 5ml/kg, abdominal distention (see appendix for definitions).

Complicated insertion of feeding tubes: nasal bleeding

Mechanical complications Feeding tube displacement or obstruction

### **\*Complications possibly related to parenteral feeding**

Mechanical complications Occlusion and dislodging of central venous catheters

Clinical complications: pneumothorax, hemothorax and arterial puncture, central line replacement due to suspicion of catheter-related blood stream infections

### Safety endpoints

Safety endpoints comprise vital status, hypoglycaemia, SAEs and complications related to the mode of nutrition. Survival up to 90 days after randomisation in both treatment groups will be compared by Kaplan Meier survival plots. The impact of "late PN" versus "early PN" will be analysed, with and without correction for risk factors, by Cox proportional hazard analysis. In addition, we will record in-ICU and in-hospital mortality, and will analyse differences with Chi-square testing. As the

randomised study intervention only takes place during a time window up to the 8th day in ICU, we also plan to analyse early lethality within this time window in the intention-to-treat population as part of the safety analysis.

As patients not receiving early PN may be considered at increased risk for hypoglycaemia, we will report for both groups the number of patients experiencing hypoglycaemia <40 mg/dl during the time window of the randomised intervention.

Hypoglycaemia resistant to parenteral glucose administration is considered as a SAE and the incidence during the time window of the randomised intervention will be reported for both groups. In addition, overall blood glucose control during the time window of the intervention will be compared using daily morning blood glucose as well as daily maximal and minimal blood glucose.

Safety issues also comprise the occurrence of feeding-mode-related complications during the time window of the intervention. Therefore, occurrence of these complications (digestive intolerance, complicated insertion of feeding tubes, pneumothorax, haemothorax and subclavian or carotid artery puncture, occlusion or displacement of central venous catheters or gastric feeding tubes) will be reported for both treatment groups

### Interim analysis

As the previous study in adults has shown that lethality was not different among the study groups and that morbidity was prevented by withholding feeding, and since the participating centres are currently providing early PN, repeated interim analyses for efficacy are not required. However, one formal “safety” interim analysis will be planned after patient number 720 has left the ICU, during which the independent DSMB will have access to un-blinded results on ICU mortality, hospital mortality and serious adverse events. The DSMB will then judge on whether or not to prematurely stop the clinical trial for safety reasons, or to perform more safety interim analyses. The DSMB will advise on eventual continuation of the study to completion, under monitoring of the serious adverse event. Because the primary efficacy endpoint will not be analysed, no correction of the significance level at the final analysis will be necessary.

### **19.1 Section 10 WMO event**

In accordance to section 10, subsection 1, of the WMO, the investigator will inform the subjects and the reviewing accredited METC if anything occurs, on the basis of which it appears that the disadvantages of participation may be significantly greater than was foreseen in the research proposal. The study will be suspended pending further review by the accredited METC, except insofar as suspension would jeopardise the subjects’ health. The investigator will take care that all subjects are kept informed.

### **19.2 Adverse and serious adverse events**

Adverse events are defined as any undesirable experience occurring to a subject during the study, whether or not considered related to the experimental treatment. All adverse events reported spontaneously by the subject or observed by the investigator or his staff will be recorded.

A serious adverse event is any untoward medical occurrence or effect that at any dose:

- results in death;
- is life threatening (at the time of the event);
- requires hospitalisation or prolongation of existing inpatients' hospitalisation;
- results in persistent or significant disability or incapacity;
- is a new event of the trial likely to affect the safety of the subjects, such as an unexpected outcome of an adverse reaction, lack of efficacy of an IMP used for the treatment of a life threatening disease, major safety finding from a newly completed animal study, etc.

All SAEs will be reported through the web portal *ToetsingOnline* to the accredited METC that approved the protocol, within 15 days after the sponsor has first knowledge of the serious adverse reactions. SAEs that result in death or are life threatening should be reported expedited. The expedited reporting will occur not later than 7 days after the responsible investigator has first knowledge of the adverse reaction. This is for a preliminary report with another 8 days for completion of the report.

### **Safety endpoints specifically for PEPaNIC**

The clinical research team guarantees a daily follow-up of patient screening and inclusion, availability of requested clinical data in the clinical patient files and protocol compliance. Each non-compliance to the protocol and other questions or problems are reported to the study monitor and discussed with the principal investigators. Serious Adverse Events (SAE) are also reported to the study coordinating investigator/project leader (K.U.Leuven). The study monitor regularly provides the sponsor with reports on inclusions and SAE. Regular meetings are organized with principal investigators and clinical research team to discuss the daily progression of the research project.

As patients not receiving early PN may be considered at increased risk for hypoglycemia, we will report for both groups the number of patients experiencing hypoglycemia <40 mg/dl during the time window of the randomized intervention.

Hypoglycemia resistant to parenteral glucose administration, or with clinical symptoms, is considered as a SAE and the incidence during the time window of the randomized intervention will be reported for both groups. In addition, overall blood glucose control during the time window of the intervention will be compared using daily morning blood glucose as well as daily maximal and minimal blood glucose.

Further safety endpoints comprise vital status, hypoglycemia, SAEs and complications related to the mode of nutrition. Survival up to 90 days after randomization in both treatment groups will be compared by Kaplan Meier survival plots. The impact of "late PN" versus "early PN" will be analyzed, with and without correction for risk factors, by Cox proportional hazard analysis. In addition, we will record in-ICU and in-hospital mortality, and will analyze differences with Chi-square testing. As the randomized study intervention only takes place during a time window up to the 8th day in ICU, we also plan to analyze early lethality within this time window in the intention-to-treat population as part of the safety analysis.

Safety issues also comprise the occurrence of feeding-mode-related complications during the time window of the intervention. Therefore, occurrence of these complications (digestive intolerance, complicated insertion of feeding tubes, pneumothorax, haemothorax and subclavian or carotid artery puncture, occlusion or displacement of central venous catheters or gastric feeding tubes) will be reported for both treatment groups.

Above mentioned SAE's and safety endpoints will be handled and reported within the standard timeframe as described above.

#### **19.2.1 Suspected unexpected serious adverse reactions (SUSAR)**

Not applicable

#### **19.2.2 Annual safety report**

Not applicable

#### **19.3 Follow-up of adverse events**

All adverse events will be followed until they have abated, or until a stable situation has been reached. Depending on the event, follow up may require additional tests or medical procedures as indicated, and/or referral to the general physician or a medical specialist.

#### **19.4 Data Safety Monitoring Board (DSMB)**

The coordinating investigator/project leader (K.U.Leuven) provides direct access to the CRF, the source data and the study master file for monitoring, Independent Ethics committee review and regulatory inspection. The coordinating investigator/project leader (K.U.Leuven) established an independent data safety monitoring board (DSMB) (Prof. dr. [name], Prof. dr. em. [name], Prof. dr. em. [name], Prof.dr. [name] (statisticus)), which holds no conflicts of interest with the sponsor or coordinating investigator/project leader (K.U.Leuven). The coordinating investigator/project leader (K.U.Leuven) appoints one monitor. The monitor verifies that the trial is performed in accordance to the protocol as described in the European Medicine Agency's "Note for guidance on good clinical practice CPMP/ICH/135/95" as well as the Declaration of Helsinki. Monitoring will be performed and will be reported following the sponsor's standing operating procedures. No fault insurance is covered by Fortis Corporate Insurance NV (Leuven) and Akkermans Van Elten Assurantiën BV (Rotterdam).

One formal "safety" interim analysis will be planned after patient number 720 has left the ICU, during which the independent DSMB will have access to un-blinded results on ICU mortality, hospital mortality and serious adverse events. The DSMB will

then judge on whether or not to prematurely stop the clinical trial for safety reasons, or to perform more safety interim analyses. The DSMB will advise on eventual continuation of the study to completion, under monitoring of the serious adverse event. Because the primary efficacy

endpoint will not be analyzed, no correction of the significance level at the final analysis will be necessary.

The advice(s) of the DSMB will be notified upon receipt by the sponsor to the METC that approved the protocol. With this notification a statement will be included indicating whether the advice will be followed.

## 20. STATISTICAL ANALYSIS

### 20.1 Descriptive statistics

The current statistical analysis plan comprises the primary and secondary clinical endpoints of this RCT (work package 1). These include the acute clinical effects of the intervention during ICU stay and hospitalization, including survival up to 90 days after randomization.

The sample size (N=1440, 720 per arm) is calculated in order to detect, with at least 80% power (one- tailed; the two-tailed power is 70%) and 95% certainty, a reduction in PICU infections from 20% to 15% and, with at least 90% power (2-tailed) and 95% certainty, a reduction in mean duration of stay in PICU of 1 day. With this sample size, and for safety reasons, also any substantial impact on mortality (increase or decrease with an absolute  $\pm 2\%$ , although unexpected taken the adult data), can be excluded with a power of around 62-75% depending on the true mortality in the total population. We plan to calculate the true power of the study for detection of any eventual smaller differences in these outcomes.

### ***General rules of the statistical analysis***

All analyses will be done on intention to treat basis. The analyses will be performed on the whole set of patients and by subgroups of patients based on the primary diagnostic categories used as prognostic factors for stratification and on septic/non-septic groups of patients.

A consort diagram will be reported. The data file will be finalised 90 days after inclusion of the last patient. To assess compliance with the study protocol, the amounts of PN and EN actually given in the two study groups during the intervention window of 7 days will be reported as absolute numbers and percentages of target calories. Discrete variables will be summarised by frequencies and percentages and analysed by (exact) Chi- square test or logistic regression analysis. Continuous variables will be summarised by use of either mean or standard deviations (SD) or median and interquartile range as appropriate and compared using Student's t-test or Mann-Whitney-U test, as appropriate. Time to event analysis will be performed by Cox proportional hazard analysis. All outcomes will be analysed in an uncorrected manner as well as (jointly) corrected for risk factors (type and severity of illness, age, on admission nutritional status and risk scores). *A priori* defined subgroup analyses will be performed for patients admitted to ICU after cardiac surgery as compared with all other patients; for patients with and without sepsis upon admission; for patients with contra-indications for EN on admission or not. For all endpoints, differences will be considered statistically significant whenever the p-value is lower than 0.05 without correction for multiple testing.

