## **18.2 Randomisation, blinding and treatment allocation**

### ***Randomization***

The study will use a prospective, randomized, controlled, parallel-group design. On admission patients will be randomly assigned to receive EN combined with early PN or only EN. At ICU admission, consecutive patients will be randomly assigned to one of these two treatment groups using a centralized computer randomisation. Randomisation will be done in a 1:1 allocation ratio in permuted blocks of 10 (The block size remains unknown to bed-side physicians and nurses, responsible for patient recruitment and therapy assignment) and stratified according to primary diagnostic category on admission:

I Medical-ICU admissions (infectious or non-infectious): (a) respiratory (b) cardiac (c) renal (d) haematological/oncological (e) gastro-intestinal/hepatic (f) neurological (g) other.

II Surgical-ICU admissions (elective or urgent) according to referral discipline (a) cardiac surgery (b) solid organ transplants (c) pulmonary/oesophageal surgery (d) abdominal surgery (e) neurosurgery (f) trauma/orthopaedic surgery (g) burns (more than 20% BSA is burned and/or patient requires ventilation)

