#### **20.4 Interim analysis**

As the previous study in adults has shown that lethality was not different among the study groups and that morbidity was prevented by withholding feeding, and since the participating centers are currently providing early PN, repeated interim analyses for efficacy are not required. However, one formal “safety” interim analysis will be planned after patient number 720 has left the ICU, during which the independent DSMB will have access to un-blinded results on ICU mortality, hospital mortality and serious adverse events. The DSMB will then judge on whether or not to prematurely stop the clinical trial for safety reasons, or to perform more safety interim analyses. The DSMB will advise on eventual continuation of the study to completion, under monitoring of the serious adverse event. Because the primary efficacy endpoint will not be analyzed, no correction of the significance level at the final analysis will be necessary.

The safety analyses will be done on the whole set of patients and by subgroups of patients based on the primary diagnostic categories used as prognostic factors for stratification and on septic/non-septic groups of patients.

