#### *Statistical analyses*

As the sample size of the present study depended on the number of undernourished children included in the PEPaNIC-trial, we plan to perform a retrospective power analysis based on observed differences for risk of new infection as primary endpoint, rather than performing an a priori sample size calculation.

Variables will be reported as percentages, means ( $\pm$ SD) if normally distributed or as medians (IQR) if not-normally distributed. Change in weight will be reported as change in WFA or BFA SD score. Proportions will be analyzed univariably using chi-square test, means with t-test and medians with Mann Whitney test. The time-to-event effect sizes will be estimated with use of Cox proportional-hazard analysis, with data censored at 90 days. To take into account death as a competing risk for outcomes related to duration of care, data for non-survivors will be censored at 91 days. These time-to-event outcomes will be analyzed adjusted for baseline risk factors treatment center, age, diagnosis group, STRONGkids category, PIM2 score and PELOD score. The multivariable analysis of the effect of the intervention on dichotomized outcomes, adjusted for baseline risk factors, will be performed using logistic regression. Analyses regarding change in weight will additionally be adjusted for malnourishment upon admission.

P-values  $\leq 0.05$  will be considered statistically significant. P-values for interaction were calculated with the use of multivariable logistic regression analyses and multivariable Cox proportional-hazard analyses with a threshold for significance of interaction set at  $P \leq 0.10$ .

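### Section 20.1 tests each diagnostic category at p<0.05 with no interaction test: the nominal chance of at least one significant category under no effect is up to about 51% per endpoint

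*Supplement*

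**What the plan says.** The general rules in section 20.1 of the final protocol state that the analyses are done on the whole set and also "by subgroups of patients based on the primary diagnostic categories used as prognostic factors for stratification and on septic/non-septic groups of patients". The same paragraph names three binary subgroup factors as a priori: cardiac surgery against the rest, sepsis on admission, and contraindication to enteral nutrition. It ends with the decision rule: "For all endpoints, differences will be considered statistically significant whenever the p-value is lower than 0.05 without correction for multiple testing".

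Section 18.2 defines the categories. Randomisation is "stratified according to primary diagnostic category on admission", with seven medical strata, "a) respiratory (b) cardiac (c) renal (d) haematological/oncological (e) gastro-intestinal/hepatic (f) neurological (g) other", and seven surgical strata, "a) cardiac surgery (b) solid organ transplants (c) pulmonary/oesophageal surgery (d) abdominal surgery (e) neurosurgery (f) trauma/orthopaedic surgery (g) burns".

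Section 20.4 carries the split over to safety: "The safety analyses will be done on the whole set of patients and by subgroups of patients based on the primary diagnostic categories".

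Sections 20.1 to 20.4 contain no treatment-by-subgroup interaction test. The SAP does use them ("P-values for interaction were calculated with the use of multivariable logistic regression analyses", with a threshold of 0.10), but it governs a secondary analysis of undernourished children and of weight change. There, diagnosis group is an adjustment covariate and not a subgroup factor.

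**The concern.** A subgroup analysis should answer whether the treatment effect differs between kinds of patient. The plan instead tests the effect separately in each kind of patient. A p-value below 0.05 in one category and above it in another is what chance produces when the effect is the same everywhere, or absent everywhere. The significance rule covers all endpoints and makes no exception for subgroups, so the category analyses are inferential under the plan's own terms.

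The introduction presents the trial as evidence for practice guidelines. A significant result in one diagnostic category could then be read as a benefit or harm specific to that category, when the plan contains no test that would support such a reading.

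**Working it through.** **1. The plan's own figure.** Inputs from section 20.1: 720 per arm, infection 20% versus 15%. Normal approximation with pooled variance under the null:

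power = Φ{[0.05·√720 − z·√(2·0.175·0.825)] / √(0.20·0.80 + 0.15·0.85)}

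- One-tailed, z = 1.645: (1.3416 − 0.8839)/0.5362 = 0.854, power 80.3%.
- Two-tailed, z = 1.960: (1.3416 − 1.0532)/0.5362 = 0.538, power 70.5%.

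The stated 80% and 70% are reproduced. The plan states no error rate for the subgroup tests.

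**2. Nominal chance of at least one significant category.** There are 7 + 7 = 14 categories. Each child has one primary category, so the categories share no patients and the tests are independent to a close approximation. With no effect in any category and each test at true size 5%:

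1 − 0.95^14 = 1 − 0.4877 = 0.512, about 51% per endpoint.

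The septic/non-septic, cardiac-surgery and enteral-contraindication tests, and the duplicate corrected and uncorrected analyses, come on top. I have not added them, because they reuse the same children and the independence formula does not apply.

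**3. How far a binary endpoint can fall below the nominal rate.** Section 20.1 allows an exact test for discrete outcomes. The true size of each test was enumerated at an assumed 17.5% event rate (midway between 20% and 15%) in both arms, with 14 equal cells. The chance over all 14 is 1 − (1 − size)^14.

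| Per arm per category | Chi-square: size | over 14 | Fisher: size | over 14 |
|---|---|---|---|---|
| 10 | 2.6% | 30.7% | 0.6% | 7.8% |
| 20 | 5.0% | 51.3% | 2.2% | 26.5% |
| 30 | 5.0% | 51.5% | 2.0% | 24.7% |
| 51 (720/14) | 4.8% | 50.1% | 2.7% | 31.8% |

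The range is about 8% to 51%. Time to live discharge, the other primary endpoint, is analysed by Cox regression. This discreteness argument does not apply there, although no small-cell size was calculated for it.

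**4. What the rule does when the effect is real and uniform.** The step 1 formula, two-tailed, gives this power for 20% versus 15% within one category:

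- 10 per arm: 4.8%
- 25 per arm: 6.7%
- 51 per arm: 9.7%
- 250 per arm: 31.2%

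With 14 equal categories of 51 per arm, the expected number significant is 14 × 0.097 = 1.4. One or two categories would reach significance and the rest would not, although the effect is identical in all of them. This calculation does not depend on the null hypothesis.

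**The case against.** - **The 51% is a nominal rate.** This stands. It needs every test to have true size 5%, and step 3 shows that exact tests in small cells can bring it far lower. It should be quoted with its range.
- **Equal categories are unrealistic.** This also stands. Section 15.1 reports that 61% of admissions at one centre followed cardiac surgery, so one category will be large and others smaller. Category sizes are not given, and the equal cells are only illustrative. The nominal figure does not depend on them, and step 4 shows low power even at 250 per arm.
- **The 51% measures false positives under no effect, whereas the worry is false claims of difference.** That is a fair distinction. No rate of false heterogeneity claims has been calculated. Step 4 shows only that a uniform effect would give a mixed pattern of significant and non-significant categories.
- **The categories might mean only the two headed classes, medical and surgical.** The figure would then be 1 − 0.95^2 = 9.75%. Section 18.2 lists the lettered strata under the same term, so 14 is the better-supported reading.
- **The cardiac-surgery comparison may be meant as a between-group contrast.** Possibly, but no interaction test is named, and that sentence does not cover the 14 categories.
- **The plan openly declines to correct for multiplicity.** It does, but disclosure does not supply the missing test of whether effects differ.

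A reader might also infer that the same split at the safety interim carries a calculable false-alarm rate and could drive a stopping decision. The documents do not support this. Sections 19.4 and 20.4 state no test, significance level or boundary and leave the decision to the board's judgement. The subgroups overlap the whole set, and deaths per cell would be few.

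**Conclusion.** The point holds. Section 20.1 applies an uncorrected 0.05 rule inside each of 14 diagnostic categories and three further subgroup factors, and the protocol's statistical section has no interaction test. Within-category p-values do not show that the effect differs between categories.

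The size is up to about 51% per endpoint, nominally. It assumes no effect in any category, tests of true size 5%, and the 14-category reading. For a binary endpoint the figure ranges from about 8% to 51% under the assumptions in step 3.

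Three stronger readings are not supported:

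- A combined rate over both primary endpoints cannot be obtained by treating them as independent. Infection and time to discharge are measured in the same children and are plausibly correlated.
- No interim error rate can be given, for the reasons under the objection.
- The whole-population analyses of the primary endpoints are untouched. The weakness concerns only claims about categories and subgroups.

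**What to change.** In section 20.1, replace significance testing inside subgroups by one treatment-by-subgroup interaction test per factor: a single global test for diagnostic category (13 degrees of freedom for 14 categories), and one each for sepsis, cardiac surgery and contraindication to enteral nutrition. State the interaction threshold. Show each subgroup's estimate with its 95% confidence interval, labelled exploratory, and make no significance claim inside a single subgroup. In section 20.4, label the interim subgroup tables descriptive.

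At a 0.05 threshold the global test holds the error for diagnostic category at a nominal 5% per endpoint. All four tests together give at most 4 × 5% = 20% per endpoint, so the results stay exploratory.

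The cost is wording and one model term per factor, with no new data. The team already uses interaction tests in the SAP. Two limits should be accepted: significance can no longer be claimed within a single category, and very sparse categories may need a pooling rule fixed in advance so that the 13-degree-of-freedom model can be fitted.
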